### Exclusion criteria

Patients meeting any of the following criteria will be excluded:

Presence of any ischemic infarct lesions outside the brainstem on brain MRI.Pregnancy; end-stage malignancy; history of brain surgery; or prior central nervous system diseases such as epilepsy, brain tumors, or other major neurological disorders.Presence of psychiatric disorders; severe cardiac, pulmonary, hepatic, or renal dysfunction; or critical illness with unstable vital signs.Skin breakdown, infection, or other local conditions at the proposed needling sites that preclude acupuncture, or inability to cooperate with the required assessments.Presence of a cardiac pacemaker, vascular or other metallic implants, coronary artery bypass grafting, or any other condition that constitutes a contraindication to MRI.

### Withdrawal criteria

Subjects will be withdrawn from the study if any of the following occur:

Enrollment despite not meeting the predefined inclusion criteria (mis-enrollment).Failure to receive the assigned intervention as per protocol, or failure to complete study documentation in a way that materially affects outcome assessment.Poor treatment adherence or voluntary withdrawal from the study during the intervention period.Initiation, addition, or modification of other treatments during the trial that may interfere with the evaluation of study outcomes.

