### Conventional acupuncture group

Participants in the conventional acupuncture group will receive standard medical management, nursing care, routine rehabilitation, and conventional acupuncture.

For brainstem infarction and relevant comorbidities (e.g., hypertension, diabetes), both groups will receive standard medical management and nursing care in accordance with the Guidelines for Primary Care of Ischemic Stroke (2021) (28) and the Chinese Guidelines for Secondary Prevention of Ischemic Stroke and Transient Ischemic Attack 2022 (34), and according to the same institutional stroke care pathway. Standard care includes antiplatelet therapy, circulation-improving agents, maintenance of electrolyte balance, blood pressure and glucose control, and routine rehabilitation. In addition to standard stroke-related medications, symptomatic treatments and other clinically indicated medications will be prescribed according to the same institutional practice in both groups and recorded throughout the trial; for example, medications for dizziness or vertigo, which are common symptoms of brainstem infarction, will be used when clinically indicated. In both groups, routine rehabilitation will be delivered by rehabilitation therapists according to the same institutional rehabilitation protocol and individualized according to each patient’s neurological deficits. The rehabilitation program may include limb motor training, balance and gait training, activities of daily living training, swallowing training, speech- or dysarthria-related training, and other task-oriented functional exercises when clinically indicated. Throughout the study period, all concomitant medications and rehabilitation interventions, including their type or category, dose or frequency, duration, and any modification, will be carefully recorded by blinded assessors to facilitate assessment of the comparability of co-interventions between groups.

Conventional acupuncture will be administered as part of the routine integrative treatment for stroke. The selection of acupoints for conventional acupuncture will be based on the national higher education textbook Acupuncture and Moxibustion (35) and the routine clinical practice pathway of the Department of Acupuncture, The Second Affiliated Hospital of Guangzhou University of Chinese Medicine.

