### Clinical data analysis

All clinical statistical analyses will be performed by independent statisticians who are blinded to group allocation, using SPSS version 26.0 (IBM Corp., Armonk, NY, USA). The primary clinical analysis will focus on the between-group difference in BI change after treatment. Analyses of clinical outcomes will primarily follow the intention-to-treat principle, including all randomized participants according to their allocated group. A per-protocol analysis may also be conducted as a sensitivity analysis in participants who complete the assigned intervention. Missing data will be handled using appropriate statistical methods depending on the extent and pattern of missingness.

Continuous variables will be presented as mean ± standard deviation (SD) when normally distributed or as median with interquartile range (IQR) when non-normally distributed. Categorical variables will be summarized as frequencies and percentages. Between-group comparisons of continuous variables will be performed using the independent-samples t-test for normally distributed data or the Mann–Whitney U test otherwise. Within-group changes over time will be assessed using paired-samples t-tests or Wilcoxon signed-rank tests, as appropriate. For categorical or ordinal variables, the chi-square test, Fisher’s exact test, or rank-sum test will be used as appropriate. Clinically relevant concomitant medications and rehabilitation interventions will be summarized by group using descriptive statistics, with attention to the magnitude and clinical relevance of any between-group differences. If clinically meaningful imbalances in co-interventions are observed, these factors will be considered in the interpretation of the results, and exploratory sensitivity analyses or covariate-adjusted analyses may be performed as appropriate.

For repeated clinical assessments, changes over time and between-group differences will be further evaluated using repeated-measures analysis or an equivalent mixed-effects approach, where appropriate. The relationships between clinical outcome measures and imaging parameters will be assessed using Pearson or Spearman correlation analyses, depending on the distribution of the data. All statistical tests will be two-sided, and a *p*-value < 0.05 will be considered statistically significant.

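### The withdrawal criteria take randomised patients out of the study for non-adherence or treatment changes, with no stated outcome follow-up, which conflicts with the promised intention-to-treat analysis

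*Protocol article*

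**What the plan says.** The Withdrawal criteria open with a mandatory rule: "Subjects will be withdrawn from the study if any of the following occur". The triggers include mis-enrolment, "Failure to receive the assigned intervention as per protocol", documentation failures that affect outcome assessment, "Poor treatment adherence or voluntary withdrawal from the study during the intervention period", and "Initiation, addition, or modification of other treatments during the trial that may interfere with the evaluation of study outcomes". The article does not say whether a withdrawn patient is still assessed at Day 14 or at 1 month.

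Clinical data analysis sets the primary population: "Analyses of clinical outcomes will primarily follow the intention-to-treat principle, including all randomized participants according to their allocated group". A per-protocol analysis of those who complete the intervention is an optional sensitivity analysis. Missing data are to be handled by methods suited to their extent and pattern.

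The Conventional acupuncture group section, which describes co-interventions for both arms, expects treatment to vary: "medications for dizziness or vertigo, which are common symptoms of brainstem infarction, will be used when clinically indicated". Rehabilitation is individualised, and any modification of drugs or rehabilitation is recorded so that the arms can be compared. Blinding states that participants and acupuncturists are not blinded, while outcome assessors and statisticians are.

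**The concern.** The patients named in the withdrawal list, apart from those who withdraw consent, are the ones an intention-to-treat analysis exists to keep. Read by itself, the list defines a per-protocol set, but it is written as a rule for leaving the study.

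Except for mis-enrolment, the triggers arise after randomisation and can be related to both arm and prognosis. The experimental arm adds a daily session at about 15 to 20 scalp points for 14 days, so adherence may differ between arms. Patients who recover poorly are plausibly more likely to have treatment added or changed. The phrase about changes that may interfere has no operational definition, and the article does not say who makes the judgement.

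At stake is the primary between-group difference in Barthel Index change. Outcomes that are not collected cannot be recovered by any later analysis plan.

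**Working it through.** **1. The two rules side by side.** For a patient who misses sessions in week 1, the withdrawal rule takes the patient out of the study, while the analysis rule counts the patient in the allocated arm. Both can be honoured with observed data only if the Day 14 and 1-month assessments still take place, and the article does not say that they do. Otherwise the patient's Barthel Index is missing and has to be imputed or modelled.

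**2. The plan's own figures (Sample size calculation).** The inputs are a difference of 17.50 − 12.66 = 4.84, SD 5.22, two-sided alpha 0.05, power 90% and dropout 15%. The two-sample t-test needs 25.44 patients, rounded up to 26 per arm (power 90.6%). Then 26/0.85 = 30.6, rounded up to 31 per arm and 62 in total. The stated sample size is reproduced and is not in dispute. The allowance leaves room to lose 31 − 26 = 5 patients per arm.

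**3. Algebra of the bias.** If a fraction w of one arm is removed, and those patients differ by g points from the rest of that arm, the arm mean shifts by w × g. For w = 15% and assumed g of 2.5 to 10 points, the shift is 0.15 × 2.5 = 0.4 to 0.15 × 10 = 1.5 points. That is 8% to 31% of 4.84.

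**4. Simulation under no true effect.** There are 31 patients per arm with SD 5.22. Of these, 3 or 5 are removed from one arm only, and the remaining patients are compared by t-test. The strength of the link between removal and outcome is an assumption, because the documents give no figure.

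| Link between removal and outcome | Removed | Shift (points) | Share of 4.84 | Type I error |
|---|---|---|---|---|
| Correlation 0.3 | 3 of 31 | about 0.3 | 6% | 5 to 6% |
| Correlation 0.3 | 5 of 31 | about 0.45 | 9% | about 6% |
| Poorest outcomes removed (worst case) | 3 of 31 | about 0.94 | 19% | about 12% |
| Poorest outcomes removed (worst case) | 5 of 31 | about 1.46 | 30% | about 22% |

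The sign depends on the arm. Losing poor outcomes from the experimental arm flatters Shallow Acupuncture, and losing them from the control arm hides a benefit. If the poorest k are removed from both arms equally, the mean shift is zero, but type I error is still about 8% (k = 3) to 9% (k = 5).

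**5. Cost in power of keeping everyone.** Suppose all 31 per arm are assessed and 10% of the experimental arm gains nothing from the addition. The difference becomes 4.84 × 0.90 = 4.36, with power about 90%. At 15% it is 4.84 × 0.85 = 4.11, with power about 86%.

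**The case against.** A reader might infer that the intention-to-treat analysis cannot be delivered, or that it turns into an analysis of completers. The article does not support that. It never says that outcome collection stops at withdrawal or that withdrawn patients leave the analysis set. It names all randomised participants as the primary population, provides for missing data, and mentions a repeated-measures or mixed-effects approach. Follow-up after withdrawal may also be covered in a full protocol that is not shown. All of this stands, and it makes the harm conditional on follow-up ending. It does not remove the conflict: the rule as printed is mandatory, concerns the study and not just treatment, and contains no clause that keeps outcomes coming. Imputation would fill gaps that the protocol itself created, under assumptions that cannot be tested.

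A reader might also infer that the treatment-change criterion flatly contradicts the co-intervention text. The two can partly coexist: care within the institutional pathway is permitted and recorded, and only changes that may interfere lead to withdrawal. Imbalances in co-interventions are to be summarised and possibly adjusted for. What remains is that nothing separates an expected modification from an interfering one.

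Biased judgement is possible but not shown. Assessors are blinded, and they also record the co-interventions. Over 14 days of inpatient treatment, a large difference in adherence between arms is an assumption. The worst-case figures are therefore an upper bound and should not be quoted alone.

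**Conclusion.** The point holds in conditional form. The withdrawal rule and the intention-to-treat statement conflict as printed, and the article has no provision that resolves it. If follow-up ends at withdrawal, the primary analysis depends on imputed or modelled outcomes for patients who may have been selected by arm and prognosis.

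The size is uncertain. With 3 to 5 of 31 patients lost from one arm, it runs from a minor shift of about 0.3 to 0.45 points with type I error near nominal, up to about 0.9 to 1.5 points with type I error of about 12 to 22% in the worst case. These figures assume normal outcomes with SD 5.22, losses in one arm only, an analysis of the remaining patients without imputation, and the stated link between removal and outcome. The conflict between the two sections does not depend on them.

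**What to change.** - Reword the Withdrawal criteria so that mis-enrolment, deviation from the intervention, poor adherence, documentation failures and interfering treatment changes are recorded as protocol deviations or treatment discontinuation, not as withdrawal from the study.
- State that the Barthel Index, NIHSS and mRS are collected at Day 14 and 1 month in every randomised patient unless consent is withdrawn, and are analysed in the allocated arm.
- Use the present list only to define the per-protocol set.
- Reconcile the treatment-change criterion with the co-intervention text in the Conventional acupuncture group section, so that it is clear which recorded modifications count as interfering. Which clinical rule applies is for the investigators to decide.

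The cost is a wording amendment and a few more assessments at visits already in Table 1. On the figures above, keeping these patients is affordable at the planned 62. The amendment helps only patients whose outcome visits are still to come.

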### Sample size calculation

The sample size for the clinical component was calculated based on the primary clinical outcome, namely the between-group difference in Barthel Index (BI) improvement after treatment. According to previous literature (30), the mean increase in BI after conventional acupuncture was approximately 12.66 points. Because no prior study has specifically evaluated the effects of Shallow Acupuncture in patients with brainstem infarction, the expected effect size for the present study was informed by a preliminary pilot study conducted in patients with brainstem infarction treated in the Department of Acupuncture of The Second Affiliated Hospital of Guangzhou University of Chinese Medicine. In these patients, who received Shallow Acupuncture combined with conventional acupuncture, the mean increase in BI after 2 weeks of treatment was approximately 17.5 points, with a standard deviation of 5.22. The clinical sample size was estimated in PASS using the Two-Sample T-Tests Assuming Equal Variance procedure. For transparency, the conventional planning formula is shown below:

$$n=\frac{2{\left(Z_{1-\alpha /2}+Z_{1-\beta }\right)}^{2}\sigma^{2}}{\delta^{2}}$$

where n denotes the required sample size per group, *δ* denotes the expected between-group difference in BI improvement, and *σ* denotes the assumed common standard deviation. In the present study, the expected between-group difference was set at 4.84 points (17.50–12.66). Because no published estimate of the standard deviation of BI change was available for the control condition, a common standard deviation of 5.22, derived from preliminary pilot observations, was assumed for planning purposes. Using a two-sided significance level of 0.05, 90% power, and a 1:1 allocation ratio, PASS estimated that 26 participants per group (52 participants in total) would be required. Assuming a dropout rate of 15%, the final planned sample size was set at 62 patients, with 31 participants in each group.

For the neuroimaging component, a formal sample size calculation was not considered feasible because of the heterogeneity of rs-fMRI/DTI analysis methods and the exploratory nature of the imaging analyses. Therefore, the imaging sample size was determined pragmatically with reference to prior neuroimaging literature (31–33), in which 12 participants per group have often been regarded as a minimum for obtaining stable estimates. To enhance reliability and to allow for potential data loss due to motion artifacts or incomplete scans, 20 participants per group will be included in the rs-fMRI/DTI analyses.

### Randomization

A computer-generated randomization sequence will be created by an independent researcher who is not involved in participant recruitment, treatment delivery, outcome assessment, or statistical analysis. Participants will be randomly assigned in a 1:1 ratio to the conventional acupuncture group or the adjunctive Shallow Acupuncture group, with 31 patients in each group. The allocation sequence will be concealed in sequentially numbered, opaque, sealed envelopes. The envelopes will be kept by designated study personnel and opened in numerical order only after an eligible participant has been enrolled. Participants will then be assigned to the corresponding group according to the allocation indicated inside the envelope.

### Blinding

Because of the nature of the intervention, participants and acupuncturists cannot be blinded in this study. To minimize bias, several measures will be implemented. First, acupuncturists will be responsible only for treatment delivery and will not participate in participant recruitment, group allocation, outcome assessment, or data analysis. Second, all clinical outcome assessments will be performed by independent investigators who are blinded to group allocation. Third, statisticians responsible for data management and statistical analysis will remain blinded to group labels throughout the analysis process. For the neuroimaging component, imaging data processing and analysis will also be conducted by investigators who are blinded to group allocation whenever feasible.

### Interventions

All interventions will be performed by licensed acupuncturists who have completed standardized training for this trial and have at least 3 years of clinical experience. Participants in both groups will receive treatment once daily, for 2 consecutive weeks, for a total of 14 treatment sessions. In keeping with routine inpatient practice in the acupuncture department, both groups will receive standard medical management, routine rehabilitation, and conventional acupuncture. The between-group difference will be the addition of Shallow Acupuncture in the experimental arm. The overall contents of the two intervention arms are summarized in Table 2.

**Table 2 tab2:** Summary of interventions in the conventional acupuncture group and the Adjunctive Shallow Acupuncture group.

Intervention component	Conventional acupuncture group	Adjunctive Shallow Acupuncture group	Key specification
Standard medical management	Yes	Yes	Guideline-based management of ischemic stroke and vascular risk factors according to the same institutional stroke care pathway
Rehabilitation	Yes	Yes	Standard stroke rehabilitation according to the same institutional protocol
Conventional acupuncture	Yes	Yes	Once daily for 14 consecutive days; fixed prescription described in the Methods section
Shallow Acupuncture	No	Yes	Once daily for 14 consecutive days; performed at pathological response points in predefined temporal and occipital regions

### Conventional acupuncture group

Participants in the conventional acupuncture group will receive standard medical management, nursing care, routine rehabilitation, and conventional acupuncture.

For brainstem infarction and relevant comorbidities (e.g., hypertension, diabetes), both groups will receive standard medical management and nursing care in accordance with the Guidelines for Primary Care of Ischemic Stroke (2021) (28) and the Chinese Guidelines for Secondary Prevention of Ischemic Stroke and Transient Ischemic Attack 2022 (34), and according to the same institutional stroke care pathway. Standard care includes antiplatelet therapy, circulation-improving agents, maintenance of electrolyte balance, blood pressure and glucose control, and routine rehabilitation. In addition to standard stroke-related medications, symptomatic treatments and other clinically indicated medications will be prescribed according to the same institutional practice in both groups and recorded throughout the trial; for example, medications for dizziness or vertigo, which are common symptoms of brainstem infarction, will be used when clinically indicated. In both groups, routine rehabilitation will be delivered by rehabilitation therapists according to the same institutional rehabilitation protocol and individualized according to each patient’s neurological deficits. The rehabilitation program may include limb motor training, balance and gait training, activities of daily living training, swallowing training, speech- or dysarthria-related training, and other task-oriented functional exercises when clinically indicated. Throughout the study period, all concomitant medications and rehabilitation interventions, including their type or category, dose or frequency, duration, and any modification, will be carefully recorded by blinded assessors to facilitate assessment of the comparability of co-interventions between groups.

Conventional acupuncture will be administered as part of the routine integrative treatment for stroke. The selection of acupoints for conventional acupuncture will be based on the national higher education textbook Acupuncture and Moxibustion (35) and the routine clinical practice pathway of the Department of Acupuncture, The Second Affiliated Hospital of Guangzhou University of Chinese Medicine.

Body acupuncture points are selected as follows: GV20 (Baihui), EX-HN3 (Yintang), bilateral GB20 (Fengchi), bilateral PC6 (Neiguan), bilateral GB34 (Yanglingquan), CV12 (Zhongwan), CV10 (Xiawan), CV6 (Qihai), CV4 (Guanyuan), contralateral KI17 (Shangqu), and ipsilateral ST24 (Huaroumen) and ST26 (Wailing).

Procedure: with the patient in a comfortable position, the skin at each acupoint will be routinely disinfected. Disposable sterile filiform needles (Han Yi brand, 0.25 × 25 mm, 0.25 × 40 mm, or 0.25 × 50 mm; manufacturer: Changchun Aikang Medical Devices Co., Ltd.) will be inserted perpendicularly into the selected acupoints, with needle depth adjusted according to the anatomical location of each point. After the arrival of needling sensation (deqi), a neutral manipulation (neither reinforcing nor reducing) will be applied. Needles will be retained for 20 min.

### Adjunctive Shallow Acupuncture group

Participants in the adjunctive Shallow Acupuncture group will receive the same standard medical management, nursing care, rehabilitation program, and conventional acupuncture regimen as the conventional acupuncture group. In addition, they will undergo adjunctive treatment with Shallow Acupuncture.

Selection of pathological response points: Shallow Acupuncture will target pathological response points located in the temporal and occipital regions. Consistent with the concept introduced in the Introduction, pathological response points will be operationally identified as clinically detectable reactive areas within the temporal and occipital regions. These points may present with one or more of the following features: changes in skin color (e.g., pallor or darkening), abnormal hair follicle distribution (e.g., focal areas with unusually enlarged pores), alterations in the superficial vascular network (e.g., abnormal superficial arteries or veins), changes in skin tension (e.g., increased tightness on light palpation), morphological abnormalities (e.g., palpable subcutaneous nodules or cord-like structures on deep palpation), or sensory abnormalities (e.g., tenderness, soreness, or numbness).

Definition of the Shallow Acupuncture regions: Temporal region: defined in this study as the scalp area bounded superiorly by the temporal line, inferiorly by the upper margin of the zygomatic arch, anteriorly by the frontal process of the zygomatic bone, and posteriorly by the auricle and the anterior border of the mastoid process. Occipital region: defined in this study as the scalp area bounded superiorly by a horizontal line passing through the vertex of the lambdoid suture (lambda), inferiorly by a horizontal line at the level of the spinous process of the second cervical vertebra (C2), and laterally by the mastoid process and the posterior temporal line.

Standardized identification and selection procedure: Pathological response points will be identified using a standardized procedure consisting of visual inspection, palpation, and confirmation of local sensory responses. Visual features, such as changes in skin color, will be assessed and recorded when present. However, in the temporal and occipital regions, point selection will rely primarily on palpation-based and sensory features, as defined above. A point will be considered a positive pathological response point when at least one predefined pathological response feature is present. In each session, approximately 15–20 pathological response points will be selected within the predefined temporal and occipital regions, depending on the distribution of positive pathological response points. Among positive pathological response points, those with clearly identifiable palpation-based abnormalities and/or local patient-reported sensory responses during palpation will be prioritized. The number, location, and defining features of selected points will be documented at each treatment session. All acupuncturists responsible for Shallow Acupuncture will receive standardized training in the identification and documentation of pathological response points before trial initiation.

Shallow Acupuncture procedure: Patients will be placed in a sitting position with the head slightly flexed or in the prone position. After routine skin disinfection, disposable sterile filiform needles (Han Yi brand, 0.25 × 25 mm; Changchun Aikang Medical Devices Co., Ltd.) will be inserted with a transverse or oblique Shallow Acupuncture technique at positive pathological response points within the temporal and occipital regions. The needle tip will form an angle of approximately 10°–30° with the skin surface, and the needle will be advanced subcutaneously along the direction of the lesion for about 0.2–0.6 cun, approximately 4–12 mm in this protocol. Needles will be oriented toward the presumed lesion site and retained for 20 min. During needle retention, patients will be guided to perform targeted functional exercises tailored to their neurological deficits. The key procedural parameters of Shallow Acupuncture at temporal and occipital pathological response points are detailed in Table 3.

**Table 3 tab3:** Shallow Acupuncture protocol at temporal and occipital pathological response points.

Aspect	Protocol	
Target regions	Temporal region: Superior: temporal line; inferior: superior margin of the zygomatic arch; anterior: frontal process of the zygomatic bone; posterior: auricle and anterior border of the mastoid process.	Occipital region: Superior: horizontal line passing through the vertex of the lambdoid suture (lambda); inferior: horizontal line at the level of the spinous process of the second cervical vertebra (C2); lateral: mastoid process and posterior temporal line.
Definition of pathological response points	Presence of at least one predefined feature, including abnormal skin color, abnormal pore or hair follicle distribution, superficial vascular changes, changes in skin tension, palpable subcutaneous nodules or cord-like structures, and/or local tenderness, soreness, or numbness.	
Point selection rule and dose	Approximately 15–20 pathological response points per session, depending on the distribution of positive pathological response points; among positive pathological response points, those with clearly identifiable palpation-based abnormalities and/or local patient-reported sensory responses during palpation will be prioritized.	
Needling technique	Transverse or oblique subcutaneous insertion at approximately 10°–30° toward the presumed lesion site; shallow insertion depth of about 0.2–0.6 cun, approximately 4–12 mm in this protocol; needle retention for 20 min.	
Concomitant functional training	During needle retention, patients are guided to perform task-oriented functional activities tailored to their neurological deficits, such as active shoulder and elbow movements for upper-limb weakness.	
Treatment frequency and course	One session per day, 7 days per week, for a total of 14 consecutive sessions.	

